### Consent or assent: ancillary studies {26b}

Participants will be asked if they agree to use of their data should they choose to withdraw from the trial. Participants will also be asked for permission for the research team to share relevant data with people from the universities taking part in the research or from regulatory authorities, where relevant. This trial does not involve collecting biological specimens for storage.

## Interventions

### Choice of comparators {6b}

Over the last 10 years, recommendations regarding the ideal level of oxygen for resuscitation in preterm infants have changed from 100%, down to low levels of oxygen (< 30%), up to moderate concentration (30–65%) [3, 18, 20]. The most recent individual patient analysis of eight trials by Oei et al. reported that infants who were started in < 30% oxygen had significant lower 5 min SpO_2_ values compared to infants started with ≥ 60% oxygen, which was associated with increased risk of major intraventricular hemorrhage and a five times higher risk of death [34]. The authors emphasized that trials are urgently needed to evaluate the risk of using low and higher oxygen concentration in preterm infant stabilization at birth. In addition, in 2010, SpO_2_ targeting was recommended as standard of care, and this contributed to a change in clinical practice as clinicians were more likely and comfortable to start resuscitation at either 21% or titrated levels of oxygen such as 30–40% [18]. When the guidelines were again revised in 2015, the committee acknowledged that a critical knowledge gap continued to exist for the resuscitation of the preterm infants < 37 weeks [20], highlighting the need to provide more concrete guidelines.

This leaves clinicians in a challenging position. Despite the advances that have been achieved in perinatal and neonatal care, neonates are still vulnerable to the consequences of the oxidative effects from hyperoxia as well as the deleterious effects from hypoxia. A large multi-center international trial of sufficient sample size that is powered to look at safety outcomes such as mortality and adverse neurodevelopmental outcomes is required to provide the necessary evidence to guide clinical practice with confidence. The trial will be using 30% and 60% as the two starting oxygen concentrations, both of which are within the parameters of current recommendations and practice.

## Intervention description {11a}

### Setting

All participating centers will change their local hospital policy to either an initial FiO_2_ of 0.3 or 0.6 as per randomization for the first cohort of infants. To enroll the next cohort, participating centers will change their local hospital policy to the other arm with initial FiO_2_ of 0.3 or 0.6.

### Treatment arms

#### ***Initial FiO***_***2***_*** of 0.3 arm***

Infants randomized to this arm will receive initial FiO_2_ of 0.3 oxygen during the first 3 min of life. Focus will be on providing effective ventilation. During this time, if SpO_2_ is available and reliable, oxygen may be increased by 20% every minute if an SpO_2_ ≥ 85% is unlikely to be achieved by 5 min. Once a reliable SpO_2_ reading is available, or at the latest at 3 min of age, the clinical team will assess SpO_2_. If SpO_2_ is < 85%, oxygen should be increased by 20% every 60 s to achieve SpO_2_ ≥ 85% at 5 min of age. If SpO_2_ is > 95% at or before 5 min of age, oxygen should be decreased by 10–20% every 60 s to maintain SpO_2_ of ≥ 85%. At 10 min of age and beyond, aim for SpO_2_ of 90–95% or as per institutional guidelines. If, at any time during the resuscitation, the heart rate (HR) is 60–100 and not increasing with effective ventilation, oxygen will be increased by 20% every minute, regardless of SpO_2_ (Fig. 1).

**Fig. 1 Fig1:**
[figure not shown]
Hi-Lo algorithm

#### ***Initial FiO***_***2***_*** of 0.6 arm***

Infants randomized to this arm will receive initial FiO_2_ of 0.6 during the first 3 min of life. Focus will be on providing effective ventilation. During this time, if SpO_2_ is available and reliable, oxygen may be increased by 20% every minute if an SpO_2_ ≥ 85% is unlikely to be achieved by 5 min. Once a reliable SpO_2_ reading is available, or at the latest at 3 min of age, the clinical team will assess SpO_2_. If SpO_2_ is < 85%, oxygen should be increased by 20% every 60 s to achieve SpO_2_ ≥ 85% at 5 min of age. If SpO_2_ is > 95% at or before 5 min of age, oxygen should be decreased by 10–20% every 60 s to maintain SpO_2_ of ≥ 85%. At 10 min of age and beyond, aim for SpO_2_ of 90–95% or as per institutional guidelines. If, at any time during the resuscitation, the HR is 60–100 and not increasing with effective ventilation, oxygen will be increased by 20% every min, regardless of SpO_2_ (Fig. 1).

### Duration of treatment period

The study intervention duration will be the first 10 min after birth.

### Criteria for discontinuing or modifying allocated interventions {11b}

If HR < 60 at any time despite 30 s of effective ventilation, oxygen will be increased to FiO_2_ 1.0, and resuscitation guidelines will be followed (including chest compressions and epinephrine) (Fig. 1).

### Strategies to improve adherence to interventions {11c}

These include a site initiation visit and training logs, followed by continuing engagement with each site during zoom investigator meeting, annual in-person trail meeting, and monthly trial newsletters.

### Relevant concomitant care permitted or prohibited during the trial {11d}

The intubation of an infant for the sole purpose of prophylactic surfactant administration in a spontaneously breathing infant reaching target saturations will not be allowed in the first 10 min after birth. Other than attempting to achieve the 5-min SpO_2_ targets, all delivery room interventions will follow the center’s local hospital policy (standard hospital practice guideline) and the current neonatal resuscitation guidelines [3, 4].

### Provisions for post-trial care {30}

Care during the primary hospitalization and after post discharge will adhere to local practice guidelines.

## Outcomes {12}

### Primary outcome

The primary outcome will be a composite outcome of all-cause mortality or the presence of a major neurodevelopmental outcome between 18 and 24 months corrected age defined as any one of the following: (i) cerebral palsy with an inability to walk unassisted; (ii) major developmental delay involving cognition or language; or (iii) visual (cannot fixate/legally blind, or corrected acuity < 6/60 in both eyes) or hearing impairment (requiring a hearing aid or cochlear implants).

Between 18 and 24 months corrected age, the infant will be assessed for cerebral palsy, developmental delays, vision, and hearing impairments. An infant who has been diagnosed as having cerebral palsy and assigned a Gross Motor Functional Classification Score (GMFCS) of 3 to 5 will be identified as having an inability to walk unassisted. Infants will be assessed using the Bayley Scales of Infant Development-4th edition (Bayley-IV) to determine major developmental delays related to cognition and speech. A cognitive or language composite score < 70 will be defined as a major delay. Any death following their first discharge home but before the scheduled 18–24-month follow-up visit will also be included in the primary outcome. The Ages & Stages Questionnaires®, 3rd Edition (ASQ-3™, by Squires & Bricker, https://agesandstages.com/products-pricing/asq3) will be an alternative to assess neurodevelopmental outcomes if a child cannot be tested with the Bayley-IV (e.g., pandemic, travel restrictions) [39]. In those cases, the ASQ-3 will be used as an alternative, and sections contributing to cognition and language will be used to determine the level of delay. The ASQ-3 has a similar predicative values and validity to Bayley-III test [40]. Furthermore, to mitigate the problem of higher-than-expected rate of missing values for the primary outcome, the HiLo trial will publish the results of in-hospital mortality (secondary outcome) and severe brain injury on cranial ultrasound (secondary outcome) before the primary composite outcome of all-cause mortality or the presence of a major neurodevelopmental outcome. This will assure a close to 100% ascertainment and prevent the HiLo trial from falling below 100% of achieved sample size, to avoid that trial results become progressively more fragile, and a random or non-random imbalance in the primary outcome among participants with missing values could erase an apparently statistically significant result [41–43].

### Secondary outcomes

Secondary outcomes include the following:Individual components of the composite primary outcomesAll-cause in-hospital mortalitySevere brain injury on cranial ultrasound: severe grade 3 and 4 intraventricular or intraparenchymal hemorrhage according to Papile [44], periventricular leukomalacia, or ventriculomegaly based on neuroimaging studies (timing and frequency of imaging based on local site practices)Bronchopulmonary dysplasia at 36 weeks corrected age and at 40 weeks corrected age, defined as receiving any supplemental oxygen or any form of respiratory support (including invasive mechanical ventilation, non-invasive ventilation with continuous positive airway pressure, nasal intermittent positive pressure ventilation, or high-flow nasal canula)Severe retinopathy of prematurity (stage 3 or higher) as defined in the International Classification of ROP and/or ROP treated with laser, cryotherapy, or intraocular injection therapy [45]Necrotizing enterocolitis, Modified Bell’s criteria stage 2 or greater [46]Total duration of mechanical ventilation via an endotracheal tube in daysDischarge home on oxygenDuration of any positive pressure respiratory support (invasive mechanical ventilation, non-invasive ventilation with continuous positive airway pressure, nasal intermittent positive pressure ventilation, or non-invasive neural assist ventilation or non-invasive high frequency ventilation, or high-flow nasal canula) in daysDuration of supplemental oxygen in daysLength of hospital stay in days*Z*-scores for weight, length, head circumference, and body mass index at 36 weeks’ post-menstrual age [47]Differences in oxygen saturation at 3, 5, and 10 min of ageProportions of infants at 3 and 5 min who are breathing spontaneously or receiving mask ventilationProportion of infants receiving FiO_2_ 1.0 during first 10 min of resuscitationProportion of infants needing to escalate oxygen concentration beyond allocated intervention arm in first 10 min after birth

## Participant timeline {13}

**Table Taba:** 

	**Enrolment**	**Allocation**	**Post-allocation**		**Post-discharge**
**Time point**	Antenatal	At birth	7–10 days of age	Hospital discharge	24 ± 6 months’ (corrected for prematurity)
**Enrolment**					
Eligibility screen	X	X			
Informed consent			X	X	
Maternal demographic and pregnancy data			X		
Randomization data		X			
Baseline infant data			X	X	
**Interventions**					
Intervention		X			
**Outcome assessments**					
Safety assessment in-hospital mortality (part of primary outcome)		X	X	X	X
Safety assessment intraventricular hemorrhage			X		
Completion of admission data				X	
**Primary outcome: neurodevelopmental assessment at 18–24 months corrected age**					X

### Sample size {14}

A sample size of 1200 (600 per group, adjusted for 10% loss of follow-up) infants has been determined based on: baseline outcome rate of 35% (18% mortality and 17% abnormal neurodevelopmental outcomes) [48], RRR of 25%, type I error of 5%, power of 80%, within-cluster within-period ICC of 0.034, within-cluster between-period ICC of 0.029, cluster size in each arm of 10–80 (unequal cluster period but equal cluster size), and loss to follow-up rate of ~ 10%. ICCs were derived from existing data from the Canadian Neonatal Network sites [48]. With these assumptions, we will need up to 20 centers (clusters) to recruit 20–80 patients per arm (20–160/center) for a total of 1200 neonates at all sites.

### Recruitment {15}

All centers were carefully selected as they have previously participated in large randomized trials and have the documented capability of enrolling the required number of infants. All participating centers will change their local hospital policy to either 30 or 60% oxygen as per randomization for the first cohort of infants. As units will switch their policy of initial oxygen concentration for the study period, it is very unlikely that non-compliance will be an issue; however, we will monitor and record carefully. This approach allows all infants born at each center, being automatically included in the trial. The consent approach for the HiLo trial will be unambiguous and acceptable for all participating centers by obtaining individual consent after birth for data inclusion in the trial and follow-up, which will strengths the number being recruited.

The number of infants being recruited will vary between 10 and 70/year depending in the size of the center. The overall recruitment period is a max of 24 months per center; however, if a center reaches their target for the first arm prior of 12 months, the center will switch to the 2nd arm. We estimate ~ 1120 infants being recruited in Canada, ~ 60 infants in Ireland, and ~ 120 infants in Spain.

## Assignment of interventions

### Allocation

#### Sequence generation {16a}

The randomization schedule (as to what will be the first arm a site will be randomized to) is provided by the Biostatics unit, at the Women and Children’s Health Research Institute (WCHRI), University of Alberta, Edmonton, Canada. Before the start of the trial, the statistician will use computer-generated random numbers to prepare the allocation sequence for all participating centers by producing the codes and allocation table, which then will be validated by an independent statistician. Each site will be allocated to either 30% in the first period and 60% in the second period or 60% in the first period and 30% in the second period with 1:1 ratio.

### Concealment mechanism {16b}

The allocation sequence for all participating sites is password protected and the password is only known to the independent statistician, the principal investigator ([name]), and the trial coordinators. Study site allocation was only communicated with each site separately after ethics approval obtained, contracts signed, and study launch confirmed.

### Implementation {16c}

Before the start of the trial, the statistician will use computer-generated random numbers to prepare the allocation sequence for all participating centers by producing the codes and allocation table, which then will be validated by an independent statistician. Clinical staff attending neonatal deliveries know the group assignment and will enroll every participant automatically, as the group assignment is also local hospital policy.

## Assignment of interventions: blinding

### Who will be blinded {17a}

Blinding will not be feasible, as each site will be assigned each study intervention arm until enrollment in the first intervention arm is complete and then switch to the second intervention arm. However, the assessors for the neurodevelopmental outcomes at 18–24 months will be blinded.

### Procedure for unblinding if needed {17b}

While each site knows their group allocation for each study period, there is no need to be unblinded for any severe adverse events (SAE). Members of the data safety monitoring board (DSMB) will have access to unblinded treatment allocation to ascertain causality for any SAE or other serious events that may be attributed to trial participation and at pre-specified intervals for interim efficacy and safety analyses.

## Data collection and management

### Plans for assessment and collection of outcomes {18a}

A manual of operation as well as work sheets have been created for training of site personal for data entry. The manual of operation includes all steps of data collection and data entry. All data entering staff have received an online seminar on how to entre data into REDCap. We have included the data collection form as appendix to this protocol. The neurodevelopmental follow-up assessment will be performed by trained psychologists, developmental pediatrician, neonatologists, or neonatal nurse practitioners, which are all trained in administering the Bayley Scales of Infant Development-4th edition (Bayley-IV). The Ages & Stages Questionnaires® will only be used if a child cannot be tested with the Bayley-IV. The ASQ-3 is a parent answered questionnaire and has a similar predicative values and validity to Bayley-III test [40].

### Plans to promote participant retention and complete follow-up {18b}

We are anticipating a ~ 10% loss to follow-up by the 18–24±﻿6 month-visit, and this has been incorporated into the sample size calculation. The centers have participated in several large neonatal trials with a neurodevelopmental follow-up component with a 3% lost-to-follow-up rate. Centers will be asked to record various contact details as allowed by their research ethics committee to facilitate maintaining contact with the infant’s family.

### Data management {19}

The HiLo investigators and research nurses at each site will be responsible for data collection which will be sourced from the paper or electronic medical charts of the mother and infant. Data will be entered into an electronic database (REDCap™, Vanderbilt University) that will be designed and managed through the University of Alberta. REDCap is a secure web application for building and managing online surveys and databases, designed to support data capture for research studies [49, 50].

### Confidentiality {27}

Participant data will be subject to data protection and privacy laws. All data will be securely stored, electronic records will only be accessible by a password known to the research team, and all data will be de-identified. Anonymity will be preserved in all scientific publications and presentations.

### Biological specimens {33}

There will be no biological specimens collected.

## Statistical methods

### Statistical methods for primary and secondary outcomes {20a}

A detailed statistical analysis plan will be finalized and submitted for publication prior to database lock. Data handling, verification, and analysis for the HiLo trial will be performed by WCHRI. Statistical analysis will follow standard methods for randomized trials, and reporting of findings will be performed in accordance with CONSORT guidelines extension for cluster trials [51].

The primary analysis will be conducted using an “intention-to-treat” approach. For the primary outcome, generalized linear mixed model with binary outcome and maximum likelihood estimate will be used to evaluate the effect of an oxygen concentration on the primary outcome. To account for cluster crossover design of the study, effects of centers (clusters) and a period (oxygen concentration) within center will be considered random, and effects of the intervention (oxygen concentration) will be entered as a fixed effect. This hierarchical model allows for the correlation of patients within periods and within clusters. The model will be adjusted for gestational age and if the infant required mask ventilation as potential confounding variables. To account for multiple births when more than one infant is enrolled in the study, clustering within mothers will be entered as a random effect in the model and this model will be tested for a better fit.

Similar generalized linear mixed models will be performed to evaluate the effect of group on secondary outcomes. If convergence problems arise, different fitting techniques will be used depending on the nature of the problem. For example, different approximation methods (e.g., maximum likelihood or pseudo-likelihood methods) will be tried; different types of covariance structures will be used. In addition, in case of singularity of variance–covariance matrix, models with fewer random effects will be created if the fit is adequate.

Analysis of secondary outcomes will use generalized linear mixed models or descriptive analysis. Summary statistics will be presented for baseline and clinical characteristics: continuous data by mean, two-sided 95% CI of the mean, standard deviation, median, interquartile range (first and third quartiles), minimum and maximum. Categorical data will be presented by absolute and relative frequencies.

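### The primary model for this two-period cluster crossover has no fixed period effect, so any common change between periods widens the standard error and, when the sequences are unequal in size, shifts the estimate

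*Protocol article*

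**What the plan says.** The protocol article, Statistical methods {20a}, states the primary model in enough detail to judge it. It is a generalized linear mixed model for a binary outcome, fitted by maximum likelihood.

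- Random part: "effects of centers (clusters) and a period (oxygen concentration) within center will be considered random".
- Fixed part: "effects of the intervention (oxygen concentration) will be entered as a fixed effect".
- Covariates: "The model will be adjusted for gestational age and if the infant required mask ventilation as potential confounding variables".
- Secondary outcomes get similar models.
- No fixed term for period or calendar time appears anywhere in the article.

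Sequence generation {16a} gives each center one of two orders: "30% in the first period and 60% in the second period or 60% in the first period and 30% in the second period". Recruitment {15} lets a period end early: "if a center reaches their target for the first arm prior of 12 months, the center will switch to the 2nd arm". Trial status says that sites joined over time after the June 2022 start.

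On siblings, {20a} says that "clustering within mothers will be entered as a random effect in the model and this model will be tested for a better fit". It also says that, if the covariance matrix is singular, "models with fewer random effects will be created if the fit is adequate".

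**The concern.** The label in {20a} treats period and oxygen concentration as one thing. Under the two sequences in {16a} they are not: a center's first period is 30% in one sequence and 60% in the other. A crossover in two sequences exists so that a change shared by centers between periods can be separated from the treatment effect. The stated model does not make that separation.

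A shared change is plausible. Care evolves, teams learn, and a center may recruit for up to 24 months. A random center-period term has mean zero by construction, so it treats a shared shift as noise. Two things follow: the reported standard error grows, and any imbalance between the sequences moves part of the shift into the treatment estimate. The sample size is set for 80% power, so lost precision matters.

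Siblings raise a separate question. If fit decides whether their correlation stays in the model, the standard error could be too small.

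**Working it through.** **1. The plan's own figure.** Inputs from the abstract and Sample size {14}: 35% vs 26.5%, type I error 5% (two-sided assumed), power 80%, ICCs 0.034 and 0.029, 10% loss, 1200 infants, up to 20 centers. The mean center-period size is m = 1200/(20 × 2) = 30.

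- Two-proportion formula: 462 per arm, or 485 with continuity correction.
- Design effect: 1 + (30 − 1) × 0.034 − 30 × 0.029 = 1.116.
- Total: 2 × 485 × 1.116/0.9 = 1203, against the stated 1200. Without continuity correction it is 1146.

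The stated size is reproduced.

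**2. Why the standard error grows.** Let d be the shared change from first to second period and K the number of centers. The within-center difference (0.6 minus 0.3) is the treatment effect plus d in one sequence and minus d in the other, plus noise. Without a fixed period term, ±d counts as between-center noise with variance d². For equal-sized centers split 10:10:

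SE(without) ≈ √[SE(with)² + d²/K]

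With SE(with) = 0.0289 and K = 20:

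- d = 3 points: √(0.000835 + 0.000045) = 0.0297, +3%.
- d = 5 points: √(0.000835 + 0.000125) = 0.0310, +7%.
- d = 10 points: √(0.000835 + 0.000500) = 0.0365, +26%.

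**3. Simulation.** Setup: 20 centers, 600 infants per period, about 10–80 per center-period, the stated ICCs, sequences 10:10, and an ML linear mixed model on center-period proportions as an approximation to the binary model. There were 600 runs per scenario. Standard errors and type I error come from null runs, power from a true difference of 8.5 points.

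| Assumed trend | Mean SE without / with period | Type I error without / with | Power without / with |
|---|---|---|---|
| none | 0.0294 / 0.0291 | 0.052 / 0.063 | 0.835 / 0.845 |
| 5 points | 0.0310 / 0.0289 (+7%) | 0.048 / 0.048 | 0.81 / 0.87 |
| 10 points | 0.0359 / 0.0289 (+24%) | 0.032 / 0.060 | 0.69 / 0.84 |

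Monte Carlo error is about 0.01 for type I error and 0.015 for power. At 5 points the actual spread of the estimate hardly differs (0.0297 vs 0.0295), so it is the reported SE that is inflated.

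Two further checks agree:

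- Within-center differences: SE 0.0319 vs 0.0301 at 5 points (+6%) and 0.0338 vs 0.0301 at 7 points (+12%).
- Logistic mixed model, 27 evaluable infants per center-period (30 × 0.9): log-OR SE 0.148 vs 0.146 without a trend, and 0.170 vs 0.151 (+13%) at a log-odds shift of 0.35, about 7 points. With a log OR of 0.414 (35% vs 26.25%), power = Φ(0.414/SE − 1.96). This gives 0.80 vs 0.81 without a trend and 0.68 vs 0.78 with it.

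**4. Shift of the estimate.** Shift ≈ d × (share of infants in one sequence minus share in the other).

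- 12:8 split, 5 points: 5 × (12 − 8)/20 = 1.0 point. The simulated means are −0.0124 without and −0.0023 with the term, a gap of 1.0 point.
- 10:10 with unequal centers: the SD of the imbalance is 0.101 to 0.156, depending on the assumed sizes. Times 5 gives 0.5 to 0.8 points.
- Simple randomisation: SD 0.244 × 5 = 1.2 points.

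**5. Siblings.** Assume a share f = 0.15–0.35 of infants in twin pairs and a sibling ICC ρ = 0.1–0.5. With siblings in the same arm, the variance factor is 1 + fρ, from 1.015 to 1.175. The true SE is then 1.007 to 1.084 times the reported one, and a nominal 0.05 becomes about 0.052 to 0.071.

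**The case against.** **A reader might infer that time trends bias the treatment effect.** On average they do not. With 10:10 sequences the simulated null means lay between −0.002 and +0.001. Only chance imbalance moves the estimate, and 0.5–0.8 points is small beside an SE of about 3 points. An SD is also not a bound: larger shifts can occur.

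**A reader might infer a large power loss.** The 68% vs 78% contrast needs a shift of about 7 points, a fifth of the 35% event rate, between periods of at most 12 months each. Nothing in the documents supports a trend of that size. At 5 points the linear approximation still gives 0.81 without the term. That is fair, although that run counts all 1200 infants as evaluable; with 10% loss the logistic check starts at 0.80 before any trend.

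**A reader might fear false positives from the missing term.** The 10:10 results point the other way: type I error falls to 0.032 at 10 points.

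**A reader might say that allocation ignores center size.** The article is silent on stratification. It condenses a fuller protocol, so silence is not evidence.

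**A reader might take the sibling clause as the same problem, or as a rule to drop the term.** It has nothing to do with time trends and acts in the opposite direction. The text does not say what follows if fit does not improve; dropping the term is the natural reading only.

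**Could this be left to the analysis plan?** Not as it stands. The article already names the fixed and random effects and presents them as its handling of the crossover design, so this concerns what is stated.

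**Conclusion.** The point holds as one of precision and model specification. The stated model omits a fixed period effect and labels period as oxygen concentration, although the allocation makes them separate factors. The cost depends wholly on a trend that the documents do not give: essentially none without a trend, about 3% of the SE at 3 points, 6–7% at 5 points (power about 0.81 vs 0.87 in the linear approximation), and about 12–24% at 7–10 points. For a 5-point trend the chance shift has an SD of about 0.5–0.8 points under a 10:10 split and about 1.2 under simple randomisation, against a target of 8.5.

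These figures assume 20 centers, the stated ICCs and assumed center sizes. The documents do not support a claim of systematic bias. The case for change rests on the remedy being nearly free rather than on a large expected loss. The sibling point is smaller and rests on an assumed twin share and sibling ICC.

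**What to change.** - In {20a} and in the analysis plan, add period (first/second) as a fixed effect in the primary model and in the mixed models for secondary outcomes. Keep the random center and center-by-period terms.
- Remove the wording that equates period with oxygen concentration.
- State that the mother random effect is retained whatever the fit comparison shows.

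The cost is a few words and one degree of freedom. Without a trend the standard error is practically unchanged (0.148 vs 0.146), so nothing is lost if the term proves unnecessary. The change can be made now, because the analysis plan is to be finalized before database lock. The term has a limit: sites start at different dates and may switch early, so first and second period are not common calendar intervals and the term removes a calendar trend only in part.
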